### Description of the intervention

A brief life review intervention (Revie ⊕) was developed based on a literature review and a theoretical model focusing on a positive patient-centered approach. Revie ⊕ allows specialist nurses to talk about life events with cancer patients, explore how the diagnosis has changed their values and preferences, and discuss ultimate life goals or projects. As an outcome of this LRI, a booklet will be created by integrating the patient’s significant elements evoked during the intervention. The intervention is delivered by eight nurses, all of whom are certified in oncology care, have received specific theoretical and evidence-based knowledge, and have the specific skills needed to deliver a life review intervention. These nurses are part of the staff. However, these nurses have time to deliver the intervention. The intervention consists of two sessions scheduled in mutual agreement between nurse and patient, but above all favoring an appropriate time for the patient. The face-to-face interview constitutes a moment completely centered on the patient’s experience. This face-to-face interview takes place in a space reserved for this purpose. In order to conduct the interview, the nurses follow a predefined guideline that permits them to be in authentic presence with the participants. The first session (T1) lasts for approximately 60 min and allows participants to share significant events about their life history as well as supports personal development by focusing on positive changes that have occurred since the cancer diagnosis. Five domains are addressed during this session: (1) a reflection of the patient’s life story and specific significant events; (2) a focus on the positive changes that have occurred since the diagnosis; (3) an expression of the patient’s values and vision of life (accentuating the strengths and resources) and the patient’s relationship with others; (4) a discussion of significant issues (i.e., what patients want to communicate with their relatives, or determining the project, which is most important to carry out); and (5) a discussion of the patient’s deepest concerns and his/her thoughts about death and dying. Throughout the intervention, nurses value patients’ coping strategies, strengths, and resources. The changes brought about by the patients’ experience of cancer on themselves and their life vision and values as well as their relationship with others are at the center of the intervention.

At the end of the interview, the participant is asked to send pictures, poems, or drawings that he considers important to the researcher. The tape recordings of the session are transcribed by the research team. Thus, a detailed account of the patients’ life events and experiences are obtained. Based on these transcripts, a booklet is created by the research team. The booklet consists of about 12 pages in A5 format and covers four sections: (1) my significant life events and the significant persons in my life; (2) my experience of cancer; (3) my values/life vision/changes; and (4) my project(s). Each booklet is personalized by highlighting its unique style with chosen words (we strive to be as close as possible to patients’ words and expressions). According to the patients’ wishes, texts, poems, pictures, or citations are integrated into the booklet.

The second meeting (15–30 min duration) is arranged to present, complete, if necessary change, and finalize the booklet. Patients who did not send photos, poems, or any other text before can include these at this moment. Patients are fully integrated as main actors of this process. If needed, another meeting is scheduled to revise the booklet. The final version of the booklet is validated by the patient before printing and delivering.

### Data collection

A baseline assessment will take place at (T0), including collection of the participants’ demographic data and data on their religious/spiritual background, as well as medical data such as tumor type, time since diagnosis, and previous treatments.

### Outcomes measures

The outcomes measures will be collected during two stages (i.e., the pre-intervention T0 and the post-intervention T2).

#### Dignity

The Patient Dignity Inventory (PDI) questionnaire [43] was designed to assess dignity-related distress. It consists of 25 items in three subcategories: illness-related concerns, a dignity conserving repertoire, and a social dignity inventory. The items are rated on a five-point Likert scale ranging from 1 (“not a problem”) to 5 (“an overwhelming problem”). The PDI exhibits good reliability and validity (Cronbach’s coefficient alpha = 0.93), and the test-retest reliability was also good (*r* = 0.85) [44]. A French version has been translated by Gagnon [18] and validated by Chochinov and his team [45].

#### Post-traumatic growth

The Posttraumatic Growth Inventory (PTGI) [46] will be used in our study to describe the change experienced by the patient since his or her cancer diagnosis. It consists of 21 declarative statements, with responses ranking from 0 to 5 (0 = “I did not experience this change”; 5 = “I experienced this change to a great extent”). The PTGI determines five factors: appreciation of life, relating to others, personal strengths, new possibilities, and spiritual change. The PTGI exhibits good internal consistency (Cronbach’s alpha coefficient = 0.90), and an acceptable test-retest reliability (*r* = 0.71) [47]. This instrument has been translated and validated into French (Cronbach’s alpha coefficient = 0.88 and the reliability = 0.47 for the French version) [48, 49].

#### Satisfaction with life

The Satisfaction with Life Scale (SWLS) [50] is used to evaluate patients’ satisfaction with life as a whole. It assesses a given individual’s global assessment of life satisfaction, and hence allows respondents to weight domains of their lives in terms of their own values. The SWLS contains five items and uses a scale of 1–7 (1 = “strongly disagree” and 7 = “strongly agree”). Cronbach’s alpha coefficient is between 0.79 and 0.89, and reliability is *r* = 0.84 [51]. The instrument has been translated into French and Cronbach’s alpha coefficient is between 0.80 and 0.84 for the French version [52]. Reliability and validity indices were validated and compared with those of the original English version.

#### Acceptability questionnaires

The acceptability questionnaire was developed by the research team based on the literature and will be addressed to participants at T2. It uses a scale of 1–5 (1 = “strongly disagree” and 5 = “strongly agree”) to assess five items: (1) the topics discussed during the interview (facility of understanding, if the questions are intrusive, distressing, relevant), (2) the planning of the meetings (the number and spacing), (3) the environment of the intervention (comfort and appropriateness), (4) the booklet (content and presentation), and (5) more generally, whether the intervention is helpful, the satisfaction of the intervention and if the participant would recommend the Revie ⊕ to other patients.

At the end of the study, an acceptability questionnaire addressed to the nurses delivering the intervention will be administrated. The questionnaire was developed by the research team based on the literature. It uses a scale of 1–5 (1 = “strongly disagree” and 5 = “strongly agree”) to assess the same five items as the participants as well as the monitoring protocol, and the training, supervision and debriefing.

### Intervention fidelity

To obtain fidelity, a guide for conducting the intervention was created. The nurses keep the guide during the intervention. During training, the importance of adhering to this guide was emphasized. The interviews are tape-recorded. Subsequently, the research team listens to the tapes to create the booklet. If case deviations are perceived, the researcher asks the nurses to adjust their intervention delivery. Regular meetings between researcher and nurses are planned in which nurses can also express their feelings and views. Finally, the nurses keep a personal diary and can add comments regarding difficulties or barriers to maintain intervention fidelity. At the end of the empirical phase, the diaries will be analyzed.

### Qualitative part

At the end of the intervention and after completing the post-test questionnaires (T2), a semi-structured interview will be conducted by the researcher, which lasts for about 30 min. This interview focuses on the experience of the intervention and the process.

The following questions are addressed: “You shared your life perspectives and finalized a booklet. What do you think and feel about the whole experience and the process? What feelings did you experience most intensely during the process?”

The nurses are also invited to keep a notebook in which they can note their difficulties and their emotions. These writings will be transcribed and a thematic analysis will be performed. To gather more detail about their intervention experience, a focus group will be led by two facilitators who are external to the research.

### Data analysis

The protocol is drafted in accordance with the SPIRIT 2013 statement [53].

#### Quantitative part

Data analysis will be performed using Stata Software Stata©. Descriptive statistics (mean, median, standard deviation) will be calculated for sociodemographic data. Analyses will be carried out on all available patient data with data at baseline and at the end of the study intervention. We will report descriptive findings concerning recruitment numbers, completions, drop-out rates, and missing data. Quantitative data will be cleaned, i.e., checked for out of range values and missing values. For >10 % of missing values, the subject will not be considered. Distribution of variables will be checked for normality using box plot, skewness and kurtosis, and test of normality. The data will be summarized with standard descriptive measurements. Continuous variables will be summarized by their mean and standard deviation, categorical variables as numbers and percentages, and presented with 95 % confidence intervals.

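### The 10 % missing-value rule excludes whole patients without saying 10 % of what, and it works badly on either reading

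*Protocol article*

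**What the plan says.** The Quantitative part of the Data analysis section states the rule in one sentence, after the description of data cleaning: for more than 10 % "of missing values, the subject will not be considered". It does not say whether the 10 % is a share of one scale, of one visit's questionnaires, or of all items at both visits. Nor does it say whether the patient leaves one analysis or all of them.

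The rule has to serve three instruments of very different length, each given at T0 and T2:
- PDI (section Dignity): "It consists of 25 items in three subcategories".
- PTGI (section Post-traumatic growth): "It consists of 21 declarative statements".
- SWLS (section Satisfaction with life): "The SWLS contains five items".

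Under Aim/objectives, estimating the sample size of a later effectiveness trial is a primary objective. Choosing the most suitable outcome for that trial is a secondary one.

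**The concern.** A percentage cut needs a denominator, and here the choice decides who is analysed. Two analysts who both follow the sentence could work with different patients.

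The whole-patient unit makes this worse. On the harshest reading, one skipped SWLS item at one visit discards that patient's complete PDI and PTGI at both visits. The shortest instrument then largely decides whose data survive on the other two.

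At stake are the pre-post means and SDs of the three scales. They are meant to inform the size of the next trial and the choice of its outcome. With 40 patients at most, avoidable losses widen every interval. Skipped items may also be related to poor health, so the remaining set may be selected.

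**Working it through.** **Inputs.** Items: PDI 25, PTGI 21, SWLS 5 (outcome sections), so 51 per visit and 102 over T0 and T2. Cut: more than 10 % (Quantitative part). Completers: 80 % of 40 = 32 (Aim/objectives). The article states no figure for the loss caused by this rule, so there is nothing to reproduce.

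**Step 1: where the cut falls.** The largest tolerated number of blanks is the largest m with m/k ≤ 10 %.

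| Denominator | k | Tolerated | First breach |
|---|---|---|---|
| PDI | 25 | 2 (8 %) | 3 (12 %) |
| PTGI | 21 | 2 (9.5 %) | 3 (14.3 %) |
| SWLS | 5 | 0 | 1 (20 %) |
| All items, one visit | 51 | 5 (9.8 %) | 6 (11.8 %) |
| All items, both visits | 102 | 10 (9.8 %) | 11 (10.8 %) |

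Per scale, the SWLS tolerates no blank and the other two tolerate two. Pooled, a wholly blank SWLS passes: 5/51 at one visit, or 10/102 if blank at both, each 9.8 %.

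**Step 2: chance of a breach.** The article gives no item non-response rate. Assume each item is blank independently with probability p. The chance of a breach on one scale at one visit is then P(X ≥ m + 1), with X binomial (k, p). For the SWLS this is 1 − (1 − p)^5; at p = 2 %, 1 − 0.98^5 = 9.6 %.

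| p | PDI | PTGI | SWLS | Any scale, one visit | Any scale, either visit | Of 32 completers |
|---|---|---|---|---|---|---|
| 1 % | 0.2 % | 0.1 % | 4.9 % | 5.2 % | 10 % | about 3 |
| 2 % | 1.3 % | 0.8 % | 9.6 % | 11.5 % | 22 % | about 7 |
| 3 % | 3.8 % | 2.4 % | 14.1 % | 19.4 % | 35 % | about 11 |

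The any-scale figure at one visit is 1 − (1 − PDI)(1 − PTGI)(1 − SWLS). At p = 2 % this is 1 − 0.9868 × 0.9919 × 0.9039 = 0.115. Over two visits it is 1 − (1 − 0.115)² = 0.217.

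**Step 3: the pooled reading.** At p = 2 %, the chance of 6 or more blanks among 51 is 0.05 % per visit. The chance of 11 or more among 102 is 0.03 % even at p = 3 %. Practically no completer is lost.

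**Step 4: which scale drives the loss.** At p = 2 % over two visits, the SWLS alone is breached by 1 − (1 − 0.0961)² = 18.3 % of patients. The PDI is breached by 1 − (1 − 0.0132)² = 2.6 % and the PTGI by 1 − (1 − 0.0081)² = 1.6 %.

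**Step 5: effect of allowing one SWLS blank.** At p = 2 %, the chance of two or more blanks is 1 − 0.98^5 − 5 × 0.02 × 0.98^4 = 1 − 0.9039 − 0.0922 = 0.4 % per visit, against 9.6 % when none is allowed.

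**The case against.** The strongest reply is that this is a clarification point about secondary, descriptive outcomes in a single-group feasibility study, and that a condensed article may leave scoring detail to a fuller document. The per-scale and pooled criticisms cannot both apply, and the large losses belong only to the harshest reading. The non-response rates are assumed, and independence is a simplification: if blanks cluster in a few patients, fewer patients are lost at the same average rate. All of this is fair and limits the weight of the point. It does not remove it, because the article does more than omit detail. It fixes a whole-patient exclusion, and each available reading has its own defect.

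Two stronger readings are tempting, and the article supports neither.

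First, a reader might infer that the rule removes drop-outs from the feasibility counts, since a patient without T2 data has far more than 10 % missing. But the same section commits to the opposite: "We will report descriptive findings concerning recruitment numbers, completions, drop-out rates, and missing data". Aim/objectives sets the criterion on 40 recruited and 80 % finishing follow-up, not on the set left after data cleaning.

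Second, a reader might see a contradiction with "Analyses will be carried out on all available patient data". That sentence goes on to restrict the set to patients with data at both time points, and the 10 % rule narrows that set further. Patients lost before T2 are already outside the pre-post comparison by that sentence, so the 10 % rule is not what removes them.

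**Conclusion.** The point holds as a defect of moderate size in the rule for the scale outcomes. The denominator is unstated, and excluding the whole patient is needlessly costly or inconsistent whichever denominator is chosen. The threshold arithmetic rests only on the item counts in the article. The size of the loss does not: about 10, 22 or 35 % of completers (roughly 3, 7 or 11 of 32) assumes independent item non-response of 1, 2 or 3 % and removal for a breach on any scale at either visit. On the pooled reading the loss is close to nil, but patients with no usable SWLS count as sufficiently complete.

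What is affected is the set behind the pre-post means and SDs, and so the inputs to the next trial's sample size and choice of outcome. The feasibility decision itself is not shown to be affected. The correction should be made before the data are analysed.

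**What to change.** Replace the sentence with a rule along these lines:

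1. Missing items are judged separately for each scale and each visit.
2. A scale is scored by pro-rating from the answered items when a stated minimum share is answered. An 80 % minimum would serve: 4 of 5 SWLS items, 20 of 25 PDI items, 17 of 21 PTGI items (0.8 × 21 = 16.8, rounded up). This cut is a proposal and is not taken from the protocol.
3. Below that minimum, only that scale score at that visit is missing. The patient stays in the analyses of the other scales.
4. The rule has no bearing on the recruitment count or on the 80 % completion count.

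The cost is one paragraph of analysis wording and no new data. The downside is small: pro-rating assumes that the skipped items would have been answered much like the others on the same scale. Reporting how many scores were pro-rated, per scale and visit, lets readers judge that.

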#### Qualitative data

Qualitative data will be managed using MAXQDA software.

The interviews will be transcribed and an inductive thematic analysis will be performed [54]. At least two researchers will independently code the interviews [55]. Reliability will be analyzed by comparing coding among coders, and an intercoder agreement will be checked within the research team. The codes will be assigned into themes.

Using an embedded concurrent design allows qualitative data to complement quantitative data, thus giving a more comprehensive perspective on the phenomenon of the study [37]. This study will also provide data to contribute to sample size calculations for a future larger effectiveness trial.

### Ethics, consent, and permissions

Our study protocol was approved by the Cantonal Commission of Ethics of Scientific Research (reference no. 15-037; see Additional files 1, 2, and 3). All patients in the study will provide written informed consent for study inclusion and the publication of data (albeit anonymously). Given the sensitivity of the topic investigated, there is a minimal risk of disrupting the psychological and emotional comfort of the participant. Nurses who conduct the intervention have professional experience and are specialized in oncology or palliative care. This enables them to provide psychological support during and after the intervention. In the case of severe emotional reaction, an internal resource for psychological support will be offered.

### Data management

The information collected will be treated anonymously and confidentially. All collected information will be encrypted through an identification number (the participant’s name will not appear). Data will be stored in a computer database to which access will be protected by passwords known only to the investigators. Personal data can be made available confidentially for audit or inspection by authorities, and in order to verify the application of ethical principles of good clinical practice in the context of a research protocol. After the transmission of data and analysis, it will become impossible to identify patients in any published articles. All documents related to the research will be archived for 10 years.

Measures to protect the confidentiality of the research data (i.e., privacy, coding, and storage) are included in this study, and as the risk level for participants is low, a data monitoring committee (DMC) was not deemed necessary for this feasibility study.

## Discussion

This new LRI intervention, called Revie ⊕, intends to promote the dignity of patients with advanced stage cancer. This study is innovative because there is a paucity of knowledge and information regarding life review interventions focusing on a positive, person-centered approach in palliative care and how this may apply under current cancer care settings in Switzerland. Life review interventions have already proven to be effective in other countries, such as Canada, Australia, and Asia. It can be expected, therefore, that this study will provide new data that may be of specific relevance to the setting in Switzerland.

This preliminary study should inform about the recruitment process and the adherence and retention of this particularly vulnerable population. It aims to give indications about the feasibility of this innovative intervention and, eventually, how to adapt the content and duration of the intervention. We will obtain information about the helpfulness of the approach by patient questionnaires and interviews. In addition, the perspective of the nurses about the acceptability of this intervention will be elicited. Nurses will be asked to provide their views about this intimate and sensitive intervention.

The use of an embedded design is recommended for testing complex patient-centered interventions, particularly for pilot studies in which new areas are investigated. We will obtain information about the sampling, the intervention delivery, study implementation, and study outcomes and measures [56].

The data will help us to validate the instruments used and determine the required sample size. If the findings from our pilot study suggest that the trial is feasible, a future larger study will be planned to measure the effectiveness of this complex intervention. This study aims also to measure strength and promote patient dignity, rather than focusing on the problems or difficulties that patients may face. Steering the intervention towards a positive approach, that is to say the positive changes that can occur as the direct result of experiencing a cancer diagnosis, could contribute to personal development and a better overall level of satisfaction with life. Being more in tune with the values and preferences of afflicted individuals could substantially contribute to their well-being in the final stages of their lives.

### Study status

The study began in April 2015. To date, 30 participants have been recruited and 27 interventions have been performed (three interventions have yet to be delivered).

## Abbreviations

LRI: Life review intervention
PDI: Personal Dignity Inventory
PTG: Posttraumatic growth
PTGI: Posttraumatic Growth Inventory
SWLS: Satisfaction with Life Scale
WHO: World Health Organization
